## 1. Introduction

Gambling behaviors among college students have become a significant public health concern, with research indicating that this demographic is particularly susceptible to gambling-related harms [1]. Globally, approximately 10.23% of college students experience problem gambling, while 6.13% meet the criteria for Gambling Disorder (GD)—a prevalence notably higher than that in the general population [2]. Several factors contribute to this heightened risk, including increased independence, peer influence, and expanded access to gambling opportunities, all of which can lead to adverse outcomes such as academic difficulties, financial hardship, and mental health challenges [3]. Despite these risks, interventions aimed at promoting responsible gambling behaviors among college students remain limited in both scope and effectiveness.

This protocol details the implementation of a randomized controlled trial (RCT) to evaluate the efficacy of RESPONSIBLEPLAY^©^, an MTM-based intervention designed to promote responsible gambling among college students. This study addresses a critical gap in the literature by comparing the MTM-based intervention with a traditional knowledge-based approach. The findings will offer valuable insights into the effectiveness of theory-driven behavioral interventions and their potential to reduce gambling-related harm within this high-risk population.

The protocol outlines the procedures for assessing the efficacy of RESPONSIBLEPLAY^©^ in fostering responsible gambling behaviors among college students. Specifically, it aims to determine whether the MTM-based approach leads to significant improvements in gambling behaviors, as measured by the Problem Gambling Severity Index (PGSI) and MTM constructs, compared with a traditional knowledge-based intervention.

By examining the factors influencing gambling behaviors in this population, this research seeks to strengthen the evidence base for designing and implementing tailored interventions to mitigate gambling-related harms. This study’s findings will inform the development of more effective, evidence-based strategies to promote responsible gambling, enhance student well-being, and potentially extend to other at-risk populations.

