After the baseline questions, the survey includes the Problem Gambling Severity Index (PGSI) to assess the impact of gambling on various aspects of the participants’ lives over the past 12 months. This section consists of nine questions designed to evaluate the severity of gambling-related issues by examining factors such as financial strain, emotional distress, health complications, and social consequences linked to gambling behaviors. The participants rate their experiences on a scale from 0 (“Never”) to 3 (“Almost always”), providing a detailed measure of the extent to which gambling has affected their lives. This information helps classify participants as low-risk, moderate-risk, or problem gamblers based on their responses. The Problem Gambling Severity Index (PGSI) is a widely used and validated measure of gambling-related risk and severity. As a part of the Canadian Problem Gambling Index, it is commonly used in both general and college populations. The PGSI has demonstrated strong internal consistency in previous studies, with reported Cronbach’s alpha values typically ranging from 0.84 to 0.91, supporting its reliability as a measure of gambling-related risk behaviors [20].

The third section of the survey consists of 32 questions aimed at assessing the constructs of the Multi-theory Model (MTM) for both the initiation and sustenance of behavior change. These questions explore the participants’ readiness to initiate responsible gambling behaviors and the strategies they employ to maintain these behaviors over time. By focusing on the psychological, social, and environmental factors that influence behavior change, this section provides valuable insights into participants’ motivation, confidence, and commitment to adopting and sustaining responsible gambling practices. The final section of the survey collects demographic information, such as age, gender, and educational background, ensuring a thorough understanding of the participant population and enabling more accurate data analysis.

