### 3.1. Significance and Implications

This study addresses a critical gap in the literature by applying MTM constructs to promote responsible gambling behaviors among college students. Unlike knowledge-based interventions that often focus solely on raising awareness without facilitating lasting behavioral change, the MTM-based approach incorporates actionable strategies that aim to not only initiate but also sustain changes in gambling behavior. Through activities such as photovoice, journaling, and role-playing, the participants are equipped with practical tools to recognize, plan for, and maintain responsible gambling habits. These hands-on strategies encourage active participation and empower individuals to take ownership of their behavior, fostering long-term outcomes.

The anticipated outcomes of the RESPONSIBLEPLAY^©^ intervention include improvements in Problem Gambling Severity Index (PGSI) scores and enhanced MTM construct scores, thus validating the framework’s effectiveness for addressing gambling-related issues. By integrating both theoretical and practical components, the intervention ensures it can be adapted for diverse populations, settings, and types of gambling behaviors. For instance, strategies like limiting physical access to gambling opportunities or fostering peer support networks are flexible and applicable across various cultural and socioeconomic contexts, making the RESPONSIBLEPLAY^©^ intervention a potentially scalable and sustainable solution for addressing gambling issues on a broader scale.

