This study relies on the PGSI as one of the key outcome measures. While the PGSI is a widely validated and commonly used instrument, its 12-month recall period may limit its sensitivity to detecting short-term behavioral changes resulting from the intervention. To address this, we will supplement our analyses with MTM construct scores, which are specifically designed to measure short-term behavioral initiation and sustenance. Additionally, we will conduct item-level analyses of the PGSI responses (e.g., related to gambling expenditure, time lost, or emotional impact) to assess whether certain dimensions demonstrate greater sensitivity to short-term change. While the PGSI was selected for its classification utility and comparability across studies, we acknowledge that it is best suited for long-term assessments. Accordingly, we are also exploring the feasibility of a 6- to 12-month follow-up study to better align with the PGSI’s recall window and to assess sustained changes in gambling behavior. This extension will depend on participant retention and funding availability but would provide a more complete evaluation of the intervention’s longitudinal impact.

While simple randomization is used for group assignment, we acknowledge that this method may result in imbalances in baseline characteristics, particularly in smaller samples. Although reproducibility was ensured through the use of a fixed seed in SAS, future studies may benefit from using stratified or block randomization to enhance group comparability.

Lastly, the self-reported nature of gambling behaviors, while necessary for understanding personal habits and attitudes, introduces the potential for recall and social-desirability biases. The participants may underreport or overreport their gambling behaviors due to memory lapses or the desire to present themselves in a more socially acceptable light. To address these biases, future studies could incorporate objective measures or third-party reports to provide a more accurate assessment of gambling behaviors and the intervention’s impact.

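### MTM construct scores are presented as measuring gambling behaviour and as one remedy for the PGSI's long recall, but the article describes them mainly as determinants of behaviour, which the experimental arm trains directly

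*Protocol article*

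**What the plan says.** The Introduction states the aim as finding out whether the MTM-based approach "leads to significant improvements in gambling behaviors, as measured by the Problem Gambling Severity Index (PGSI) and MTM constructs", compared with the knowledge-based intervention. Both instruments are thus named as measures of gambling behaviour.

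Section 3.2 (Limitations) concedes of the PGSI that "its 12-month recall period may limit its sensitivity to detecting short-term behavioral changes resulting from the intervention". The first response offered is that "we will supplement our analyses with MTM construct scores, which are specifically designed to measure short-term behavioral initiation and sustenance". Two others follow: item-level PGSI analyses, and a possible 6- to 12-month follow-up that depends on retention and funding.

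Section 2.9 (Instrumentation) describes the 32 MTM items differently. They explore "readiness to initiate responsible gambling behaviors and the strategies they employ to maintain these behaviors over time", and give insight into "motivation, confidence, and commitment to adopting and sustaining responsible gambling practices".

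Sections 2.10 and 2.13 apply the same mixed ANOVA to PGSI and MTM scores, with a 0.05 level for every analysis. Section 3.1 anticipates gains on both instruments, "thus validating the framework’s effectiveness".

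**The concern.** A score for readiness or confidence cannot make up for a behaviour measure that responds slowly, because it measures something else. If the two are treated as interchangeable, the remedy in the Limitations does not address the problem named there.

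The problem also favours one arm. The constructs that are scored are the ones the experimental sessions set out to build. A higher MTM score in that arm is what successful teaching would produce, whether or not anyone gambles differently.

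At stake is the main conclusion. The trial asks whether gambling becomes more responsible. A flat PGSI with improved MTM scores is a foreseeable result, and the wording of the aim would let it be described as improved gambling behaviour.

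**Working it through.** The plan gives no figure of its own on this point. The check compares the passages, with some arithmetic on recall windows and on how easily an MTM difference would be detected.

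**1. What the MTM scores are said to measure**

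| Place | Description |
|---|---|
| Introduction | A measure of gambling behaviour, next to the PGSI |
| Section 3.2 | A measure of short-term initiation and sustenance of behaviour |
| Section 2.9 | Readiness, motivation, confidence, commitment, and strategies used |
| Table 2 | Construct targeted, then a mechanism, then an expected behavioural outcome, in separate columns |

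The last two rows treat the constructs mainly as causes of behaviour, and the first two treat them as behaviour. Table 2 is not perfectly clean: for participatory dialogue and behavioural confidence, the entry under behavioural outcome is itself a perception or a level of confidence. That is the same blurring.

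**2. What each arm receives**

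Sections 2.4 and 2.7 and Table 2 tie the experimental activities to all six constructs. For example, Session 1 works on behavioural confidence, which is later scored. Extra reminders between and after sessions go to the experimental arm only (section 2.4). The comparison arm is described as receiving lectures and presentations (section 2.7). A between-arm MTM difference is therefore expected by design.

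**3. What the analysis permits**

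Both instruments are tested alike at 0.05. Section 2.11 refers to a primary outcome measure, but the article does not say which one it is. It does not state how an MTM gain without a PGSI gain would be read.

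**4. How much of the PGSI window can reflect the intervention**

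Share of the window before the first session = 1 − (weeks since first session)/52. Three weekly sessions put the post-test 2 to 3 weeks after the first session, depending on how weeks are counted. The follow-up is then 10 to 11 weeks after it.

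- Post-test: 1 − 2/52 = 0.962; 1 − 3/52 = 0.942.
- Follow-up: 1 − 10/52 = 0.808; 1 − 11/52 = 0.788.

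So about 94–96% of the window at post-test, and 79–81% at follow-up, predates any intervention.

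**5. How readily an MTM difference would be detected**

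Suppose, as an assumption, that training shifts one MTM construct by the effect planned in section 2.3 (f = 0.30, three time points, correlation 0.5, non-sphericity correction 1). For the group-by-time interaction, λ = f² × N × m/(1 − ρ), with 2 and 2(N − 2) degrees of freedom.

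- N = 40: λ = 0.09 × 40 × 3/0.5 = 21.6; power 0.988.
- N = 60: λ = 0.09 × 60 × 3/0.5 = 32.4; power 0.9995.

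This shows that such a shift would almost always be significant, not that it will occur. The same formula reaches 80% power at N = 20 in total (0.812), whereas section 2.3 states 20 per group. That mismatch is a separate matter and does not affect this point.

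**6. Whether a better-placed gambling measure exists**

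The survey is completed at all three time points and opens with gambling days over the past 30 days (section 2.9). At follow-up, 8 weeks = 56 days after the intervention, so the window begins 56 − 30 = 26 days after it ended. At post-test, 14 to 21 days after the first session, 9 to 16 of the 30 days still predate the intervention. Only the follow-up value is clean. Section 2.9 gives the item's use as baseline and screening, and neither section 2.13 nor Table 3 names it as an outcome for efficacy testing.

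**The case against.** Several points can fairly be made for the plan.

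- The MTM items also cover strategies that participants use, which is closer to conduct than to attitude. This stands. It is why the items are described here as mainly, not wholly, determinants.
- The questionnaire (Supplement S4) and the comparison content (Supplement S2) are not shown. A reader might infer that no MTM item records any behaviour, or that the comparison arm never touches the constructs. Neither can be established from the article.
- A reader might also infer that an MTM gain is close to guaranteed. No effect estimate in the article supports that. Table 2 does not list every activity (the guest speaker is not mapped), most named constructs are taught in Sessions 1 and 2 and not just before the post-test, and MTM scores are measured again at eight weeks.
- The strongest reading is that the trial will report MTM gains alone as success. The text does not say so. The Introduction and section 3.1 join the two instruments with 'and', and section 3.2 speaks of supplementing. A rule for discordant results may sit in an analysis plan that is not shown.
- MTM scores are not the only remedy offered. However, item-level PGSI analyses keep the 12-month recall, and the longer follow-up is conditional, so neither fills the short-term gap.

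What remains is a conflict within the article about what its second outcome measures. An analysis plan cannot remove that while the stated aim stays as worded.

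**Conclusion.** The concern holds in a limited form. The Introduction and section 3.2 treat MTM scores as measuring gambling behaviour, while section 2.9 and Table 2 describe them mainly as determinants of it. Because the experimental arm is built on those constructs, a between-arm MTM difference is expected by design and is not in itself evidence that gambling changed. With both instruments tested at 0.05, the stated aim would allow a behavioural claim on MTM scores alone, though it does not commit the trial to making one.

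The practical weight comes from the PGSI, the only gambling measure among the named efficacy outcomes: roughly four fifths of its window at follow-up lies before the first session. The conclusion assumes that the article's account of the two arms and of the MTM items is faithful to Supplements S2 and S4. It is a change that should be made; it does not invalidate the design.

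**What to change.** 1. In the Introduction and sections 2.13 and 3.2, bring the description of the MTM scores into line with section 2.9, and class them as secondary mechanism outcomes.
2. State that a conclusion of improved gambling behaviour needs a between-arm difference in a gambling measure at the eight-week follow-up.
3. Analyse the past-30-day gambling days at that visit alongside the PGSI, and state in advance how a count bounded at 0 and 30 will be modelled.
4. State that an MTM gain without such a difference will be reported as construct change without demonstrated behaviour change.

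The cost is wording and one further analysis of data that the survey already collects. The downside is that a positive claim becomes harder to make. Gambling days also record frequency rather than harm, which is why they belong beside the PGSI and not in its place.

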### 3.3. Future Directions

The findings of this study have the potential to significantly inform both research and practice in public health interventions, particularly those focused on promoting responsible gambling behaviors. Future research could explore the integration of emerging technologies, such as mobile apps and gamified tools, to enhance participant engagement, accessibility, and long-term adherence to the intervention. For example, incorporating artificial intelligence-based tracking tools could offer real-time feedback and personalized support, allowing for the continuous monitoring of progress and tailored interventions that adapt to individual needs.

Additionally, expanding the eligibility criteria of this study to include a more diverse range of populations, such as younger students or working adults, could provide valuable insights into the intervention’s broader applicability across different age groups and socioeconomic backgrounds. This expansion would allow for a more comprehensive understanding of how the intervention performs in various contexts and life stages.

Furthermore, conducting a comparative analysis of the MTM framework with other established behavioral theories could yield a deeper understanding of the mechanisms that drive behavior change in gambling and other health-risk behaviors. By comparing MTM with theories such as Social Cognitive Theory or the Transtheoretical Model, researchers could uncover unique insights into the factors that influence responsible decision-making and sustained behavior change, potentially refining existing strategies for addressing public health challenges related to gambling.

## 4. Conclusions

The RESPONSIBLEPLAY^©^ intervention underscores the potential of theory-driven, participatory approaches in addressing gambling-related harm among college students. By integrating theoretical constructs with practical applications, this study advances the academic discourse on health behavior change and offers a replicable model for public health practitioners. The findings from this study have the potential to serve as a foundation for developing evidence-based interventions aimed at promoting responsible gambling and reducing gambling-related harm across diverse populations.

Moreover, the insights gained from this research could inform policy decisions, providing a data-driven basis for crafting policies that support gambling harm reduction. These insights could also guide future intervention designs, contributing to the creation of more tailored and effective strategies for gambling behavior change.

Furthermore, this research contributes to a broader understanding of the psychological, social, and environmental factors influencing gambling behaviors. By identifying these factors, this study fosters a more comprehensive approach to prevention and harm reduction in at-risk groups, ultimately leading to improved public health strategies and outcomes. The approach could be adapted to different contexts, broadening the reach of responsible gambling initiatives and enhancing their impact on vulnerable populations.

Beyond its theoretical significance, the proposed MTM-based intervention offers practical applicability for campus health administrators, counseling centers, and public health educators aiming to address gambling-related harm in student populations. The modular and participatory structure of the intervention makes it adaptable for group workshops, orientation programs, or digital adaptation through e-health platforms. From a programmatic perspective, the model’s focus on both initiation and maintenance constructs provides a roadmap for sustained behavior change initiatives beyond gambling potentially extending to substance use, risky sexual behavior, or digital addiction. Future research could expand this framework to more diverse student populations, incorporate longitudinal designs to assess long-term outcomes, or compare MTM with other health behavior theories (e.g., Social Cognitive Theory or Transtheoretical Model) to evaluate its relative effectiveness in various contexts.

## Figures and Tables

**Figure 1 ijerph-22-00858-f001:**
[figure not shown]
CONSORT 2010 flow diagram for the RCT [13].

**Figure 2 ijerph-22-00858-f002:**
[figure not shown]
Design to test the efficacy of the responsible gambling interventions.

**Figure 3 ijerph-22-00858-f003:**
[figure not shown]
The Multi-theory Model (MTM) of the health behavior change-based intervention framework for the initiation and sustenance of responsible gambling in college students.

**Table 1 ijerph-22-00858-t001:** Comparison of current study with prior gambling interventions.

Study/Intervention	Theoretical Framework	Delivery Format	Target Group	Outcome Measures	Duration
Neighbors et al. (2015) [8]—PNF	Normative feedback	Brief online feedback	College students	Gambling frequency, risk	One time
Larimer et al. (2012) [9]—CBT + Motivational	CBT + Motivational interviewing	In-person counseling	High-risk college students	Gambling severity, coping	Multiple sessions
Pfund et al. (2023) [7]—Meta-analysis	CBT (various models)	Mixed	Mixed populations	Problem gambling severity	Varies
Current study—RESPONSIBLEPLAY^©^	Multi-theory Model (MTM)	In-person group sessions	College students (PGSI ≥ 3)	PGSI + MTM constructs	3 weeks + follow-up

PNF = personalized normative feedback; CBT = cognitive behavioral therapy.

**Table 2 ijerph-22-00858-t002:** Alignment of intervention components with MTM constructs and behavioral outcomes.

Intervention Component	MTM Construct Targeted	Mechanism of Action	Expected Behavioral Outcome
Group discussions, photovoice, brainstorming	Participatory dialogue	Enhance understanding of pros vs. cons of responsible gambling	Increased perceived value of behavior change
Role-playing, planning activities	Behavioral confidence	Build self-efficacy to manage gambling urges	Greater confidence to engage in behavior change
Brochures, self-help apps, support resources	Changes in physical environment	Improve access to tools supporting responsible gambling	Increased use of harm-reduction strategies
Psychodrama, emotional intelligence workshops	Emotional transformation	Channel emotional energy toward positive behavioral goals	Reduced emotionally driven gambling behavior
Journaling, app-based tracking, reminders	Practice for change	Reinforce behavior through reflection and repetition	Sustained responsible gambling practice
Peer mentoring, support groups	Changes in social environment	Leverage social networks for accountability and encouragement	Social reinforcement and reduced relapse

**Table 3 ijerph-22-00858-t003:** Alignment of statistical methods with study objectives.

Statistical Method	Purpose/Objective Addressed
Descriptive statistics (means, SDs)	Summarize continuous variables such as age and baseline MTM/PGSI scores.
Descriptive statistics (frequencies, %)	Describe categorical variables such as gender, class standing, and gambling types.
Chi-Square Test	Assess baseline equivalence in categorical variables between intervention and comparison groups.
Independent samples t-test	Assess baseline equivalence in continuous variables (e.g., PGSI, MTM scores) across groups.
Two-Way Mixed ANOVA	Evaluate within- and between-group differences in PGSI and MTM constructs over time (pre-, post-, follow-up), to assess efficacy of the MTM-based intervention.
Mixed ANCOVA (if needed)	Adjust for baseline differences in key variables (e.g., age, PGSI) when detected.

